### Endpoints

The primary endpoint will be the number of RBC units transfused during the OLT procedure and in the 24 hour post-surgery period, starting from arrival at the ICU. Other efficacy endpoints are (measured during surgery and during the 24-hour period post-surgery):

• The number of transfused units of fresh-frozen plasma

• The number of transfused units of platelet concentrate

• Fibrinogen concentrate administration

• Estimated blood loss

• Antifibrinolytic drugs

• Crystalloids or colloids administered

• Other escape medication used

• Estimated ascites loss

Safety is a secondary endpoint, safety parameters recorded are:

• All (Serious) Adverse Events with special focus on thromboembolic events

• General and liver-specific laboratory parameters

• Lowest pH, Ca++, lactate, temperature (during and within the first 24 h after surgery)

• Troponin levels, ECG and hepatic vessel ultrasound results

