### Parameters during surgery

The following data will be recorded for participating patients:

– Donor characteristics

– Recipient characteristics

– Liver transplantation technique (conventional versus piggy-back)

– Use of veno-venous bypass

– Data on timing (cold-ischemia time, warm-ischemia time, duration anhepatic phase etc.)

– Surgical abnormalities and technical difficulties including heavy blood loss due to diffuse oozing or accidental vascular injury

– Ascites upon opening abdomen

– Lowest PH, Ca2+, lactate, temperature (during and within the first 24 hours of surgery)

– Transfusion requirements (during and within the first 24 hours of surgery)

– Medication (during and within the first 24 hours of surgery)

– Colloid/Crystalloid/Albumin/Gelatine infusion (during and within the first 24 hours of surgery)

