### Laboratory parameters

– Prior to the OLT, an INR measurement will be performed to check if the patient still meets the inclusion criteria. After administration of the IMP, no routine INR measurements will be performed by the anaesthesiologist during the course of surgery, since measuring the INR will likely unblind the anaesthesiologist for the intervention.

– A blinded INR measurement will be performed (see section ‘Additional Study Procedures’) by an independent assistant 30 minutes after administration of the intervention and will only be available for an independent researcher. These measurements will be used during the interim analysis.

– Troponin levels are recorded just before and after surgery at ICU admission and the day after surgery, and in case of a suspected event due to clinical symptoms or ECG abnormalities during routine testing according to routine clinical practice.

– During OLT other laboratory and coagulation measurements (with the exception of the PT) may be performed according to local practice.

– Post-operatively, laboratory measurements presented in Table 4 will be performed from day 1–7 in the first week which is currently common practice in participating centers. From the second week, these laboratory measurements are only obligatory on day 14 and 30 (within a 24 hour timeframe).

**Table 4 T4:** Laboratory parameters

**Hemostasis**	**Hematology**	**Clinical chemistry**	
Prothrombin Time	Hemoglobin (Hb)	C-reactive protein	Lactate dehydrogenase
Activated Partial Thromboplastin Time	Hematocrit	Glucose	Aspartate-aminotransferase
		Creatinine	Alanine-aminotransferase
Fibrinogen	Platelets	Urea	Alkaline Phosphatase
International Normalized Ratio	Leucocytes	Sodium	Albumin
		Potassium	Calcium
		gamma-glutamyltransferase	

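### The lactate safety parameter is defined by its lowest value, although the adverse extreme for lactate is the highest (minor)

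*Protocol article*

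**What the plan says.** The Endpoints section of the Protocol article introduces the safety variables with "Safety is a secondary endpoint, safety parameters recorded are", and one of the four bullets that follow is "Lowest pH, Ca++, lactate, temperature (during and within the first 24 h after surgery"). The section Parameters during surgery, which lists the data to be recorded, has "Lowest PH, Ca2+, lactate, temperature (during and within the first 24 hours of surgery"). The two lines differ only in spelling and in the phrasing of the 24-hour window, which I take to be the same window.

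Lactate is not named elsewhere as a measurement. Table 4, under Laboratory parameters, contains "Lactate dehydrogenase", which is a different analyte. For the operation itself that section says only: "During OLT other laboratory and coagulation measurements (with the exception of the PT) may be performed according to local practice". The same safety list in Endpoints also has "Troponin levels, ECG and hepatic vessel ultrasound results", all adverse events with special attention to thromboembolic ones, and a general laboratory item.

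**The concern.** A single word, lowest, heads a list whose members do not share an adverse direction. Low pH, low calcium and low temperature are the unfavourable extremes; for lactate the unfavourable extreme is the high one. That is general clinical knowledge and the article does not discuss it. Followed literally, the line asks for the patient's best lactate. Over a window spanning the operation and the next 24 hours, that is likely to be a value from before the rise or after clearance.

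At stake is the reading of this variable. If the arms differ in how high lactate goes during or after the operation, the recorded values could still look alike, and a null comparison might be taken as reassurance that it cannot give. Because the same wording stands in both the endpoint list and the recording list, it could also pass into data collection. A later analysis plan could not restore a peak that had not been recorded.

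**Working it through.** The plan gives no figure for lactate, so there is none to reproduce. The check has two parts.

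**1. The text**

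| Place in the Protocol article | What it gives for lactate |
|---|---|
| Endpoints, safety list | Lowest value, surgery plus 24 h |
| Parameters during surgery | Lowest value, same window |
| Table 4, Laboratory parameters | None (lactate dehydrogenase only) |
| Laboratory parameters, tests during surgery | Optional, by local practice; no peak defined |
| Table 1 and Additional study procedures | No lactate schedule |

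Both places that name lactate put it under the same adjective. No section names a highest, peak or serial value.

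**2. What the lowest value can and cannot show (assumed lactate values throughout)**

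*Two patients.* Let patient A have lactate 1.5, 9 and 1.8 mmol/L at the start, after reperfusion and at 24 h, and patient B 1.5, 3 and 1.8.
- Lowest value: A = 1.5, B = 1.5, difference 0.
- Highest value: A = 9, B = 3, difference 9 − 3 = 6 mmol/L.
- If the starting value falls outside the window, the lowest is 1.8 for both and the difference is still 0.

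*Two arms.* Inputs:
- 63 patients per arm: the planned 70 per group less the 10% loss stated under Sample size, 70 × 0.9 = 63.
- Assumed mean course over seven time points: 1.5, 2.5, 4.5, 5.0, 3.5, 2.5, 1.8 mmol/L.
- Assumed log-scale SD: 0.35 between patients, 0.20 within patients.
- One arm multiplied by 1.3 at the time points stated below.
- Mann–Whitney test at two-sided 5%; 1,000 simulated trials per row.

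| Where one arm is 30% higher | Lowest of mean course | Highest of mean course | Power, lowest value | Power, highest value |
|---|---|---|---|---|
| Around the peak only (points 3–5) | 1.5 → 1.5 | 5.0 → 6.5 | 4.7% | 95.2% |
| From the peak to the end (points 3–7) | 1.5 → 1.5 | 5.0 → 6.5 | 8.2% | 95.7% |
| At every time point | 1.5 → 1.95 | 5.0 → 6.5 | 95.2% | 94.9% |

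The columns for the mean course explain the pattern. A rise that leaves the low point untouched does not move the minimum, so power stays at or near the 5% error rate. A rise that includes the low point moves the minimum and the maximum by the same factor, and both detect it equally well. The percentages depend on the assumed course. The direction follows from the definition of a minimum.

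**The case against.** **The wording may not mean what it seems to.** The line is shorthand. Lowest could attach to pH alone, and a clinically minded site might record the highest lactate anyway; the repetition may be a copied line. This is fair as to intent, but it does not rescue the text. If lowest belongs only to pH, then calcium, temperature and lactate have no stated summary. Under either reading the line needs rewording.

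**A reader might infer that the peak is discarded and captured nowhere.** The documents do not support that. The article condenses a full protocol, and neither that protocol nor the case record form is shown. Endpoints has a general laboratory item, and other tests during surgery are allowed. What stands is narrower: the article names no peak lactate, and where it fixes a summary it fixes the wrong one. That is a stated rule pointing the wrong way, not a detail left to another document.

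**A reader might infer that this variable cannot show hypoperfusion or ischaemic harm at all.** That is too strong. The last row of the simulation shows that a rise present throughout the window lifts the minimum as much as the maximum.

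**A reader might infer that the trial's watch for thrombosis is compromised.** The article gives lactate no such role; it sits in a general physiological list. Thrombotic and ischaemic harm is followed directly by:
- adverse event surveillance;
- troponin before surgery, at ICU admission and the next day;
- ECG before the intervention and on days 3 and 7;
- hepatic vessel ultrasound within 24 hours and on days 3 and 7;
- physical examination on days 3 and 7, with imaging on suspicion.

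Lowest pH, in the same bullet, gives indirect information on acidosis. This objection stands in full and sets the severity.

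**Conclusion.** The point holds as a minor one. In both places where the article defines the lactate variable, the definition read as written selects the favourable extreme. The variable would therefore largely miss a transient or late rise: in the illustration, 5% to 8% power against about 95% for the highest value. It would not miss a rise lasting the whole window.

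The effect stops at this one secondary safety variable. No lactate-specific test, threshold or stopping rule is stated, and the primary endpoint and sample size do not depend on it. The conclusion rests on the literal reading of the two lines and on high lactate being the adverse direction. The power figures also rest on an assumed lactate course and serve only to show the contrast.

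**What to change.** In Endpoints and in Parameters during surgery, replace the line with *lowest pH, Ca++ and temperature; highest lactate*, over the same window. Make the same change in the case record form if it carries the current wording. Summarise highest lactate by arm with the other safety parameters.

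The cost is a few words in two places and possibly one field label. The change concerns which of the measured values is written down, so it calls for no added blood sample or visit and does not touch patient care. It is best made before data are collected, because a peak that was not entered may not be recoverable from the trial data.

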### Study subjects

Adult patients on the waiting list for liver transplantation because of cirrhotic liver disease and a prolonged INR (≥1.5) will be asked for informed consent. Inclusion and exclusion criteria are summarized in Table 2. Upon admission in the participating center for OLT, the inclusion and exclusion criteria and the informed consent will be double-checked. Patient with co-morbidities or a medical history that increases the risk for bleeding or thrombotic events during and after OLT will be excluded from participation. All patient characteristics, including demographic data, medical history and type of liver disease will be recorded. Participating patients will be monitored in a follow up of 30 days after inclusion.

**Table 2 T2:** Inclusion and exclusion criteria

**Inclusion criteria**	**Exclusion criteria**
Age ≥18 years	Previous liver transplantation
Eligible for OLT	Split liver transplantation
INR ≥1.5	Heterotopic liver transplantation
Written informed consent	Scheduled multiorgan tranplantation
	Scheduled living-donor transplantation
	Renal insufficiency requiring dialysis
	Documented congenital coagulation disorders
	Documented history or presence of arterial or venous thrombosis
	Treatment with vitamin K antagonists
	TIPS (transjugular intrahepatic portosystemic shunt)
	Fulminant hepatic failure
	Documented coronary artery disease
	Documented thrombophilia

### Randomization and blinding

The surgical and anesthesiological team must remain blinded for the intervention during the entire duration of the trial. Randomization will be performed using an randomization website. We will stratify per center, and for patient age and gender. Randomization and preparation of the Investigational Medical Product (IMP), whether this is PCC or placebo, will be performed by an independent employee who is not involved in this trial, in the OLT or in post-operative care. The IMP will be delivered in a blinded syringe to the anaesthesiologist and administered by the anaesthesiologist.

### Intervention and dosage

The IMP will be administered during induction of anaesthesia, maximum 30 minutes prior to incision. The IMP, whether this is PCC or placebo will be administered according to the SPC of Cofact®/PPSB-D, intravenously and with a recommended infusion speed of 2 ml per minute. The dosage will be determined according to bodyweight, preoperative INR and target INR (≤1.5), as recommended in the SPC of Cofact® and as illustrated by Table 3. The same calculated dosage applies for the placebo.

**Table 3 T3:** Dosing of PCC according to INR and bodyweight to reach an INR < 1.5

**Body**	**Initial INR**												
**weight**	**4.8**	**4.2**	**3.6**	**3.3**	**3.0**	**2.8**	**2.6**	**2.5**	**2.3**	**2.2**	**2.0**	**1.8**	**>1.5**
50 kg	60	50	50	50	40	40	30	30	30	30	30	20	20
60 kg	70	60	60	60	50	50	40	40	40	30	30	20	20
70 kg	80	70	70	70	60	60	50	40	40	40	30	30	20
80 kg	90	90	90	80	80	70	60	50	50	40	40	30	20
90 kg	100	90	90	90	80	80	70	60	50	40	40	30	20
100 kg	100	100	100	90	90	80	70	70	60	50	50	30	20

The dosages are calculated based on the factor IX concentration in PCC (the above dosage refers to ml of PCC). Calculated amounts are rounded mathematically on multiples of 10 ml and an upper limit of 60 or 100 ml in total was set (see tables above). The target INR values are recommended by the Federation of Dutch Thrombosis Services and are of the same order as English and German recommendations.

### Transfusion guidelines

The following guidelines have been established for homogenous transfusion policy in all participating centers:

• Fresh frozen plasma: During surgery the use of fresh frozen plasma is allowed in

• case of ongoing bleeding and hypocoagulability indicated by TEG or ROTEM as evaluated by the responsible anesthesiologist. Type of FFP, number of units and volume will be recorded in the case record form (CRF).

• RBC transfusions when hematocrit <25%: Adjustment can be performed at several time points; the units given before surgery do not count for the endpoint calculations, only those given during and directly after surgery (within 24 h of arrival at ICU) count for determination of endpoint. Number of units and volume of transfusion will be recorded in the CRF.

• Phlebotomy when hematocrit >30%: If the hematocrit post-operatively remains

• persistently elevated above 30, a phlebotomy will be performed to lower the hematocrit if the patient is stable and does not have an active bleeding.

• Platelet concentrate: Administration is permitted when platelet counts fall below 50,000/mm^3^ and in the presence o^f^ ongoing blood loss or if it is found necessary e.g. to prevent bleeding during OLT. Type, units and volume of platelet concentrate will be recorded in the CRF.

• Fibrinogen concentrate: Administration is permitted when fibrinogen levels are < 1.0

• g/L in the presence of ongoing blood loss. = > Transfuse 30 mg/kg.

• Tranexamic acid: During the procedure TEG of ROTEM will be used to evaluate fibrinolytic potential during the procedure (see chapter 7.1.3). Upon detection of hyperfibrinolysis on the TEG or ROTEM device in presence of ongoing bleeding due to presumed coagulopathy, a bolus of 1 gram tranexamic acid will be given. The bolus can be repeated in case of insufficient effect on TEG/ROTEM and clinical picture.

• Other transfusion products will be given according to the standard procedures at the individual liver transplantation centers.

• Topical hemostatic agents: Whenever clinically indicated topical administration of hemostatic drugs/agents (e.g. collagen) is allowed (recorded as concomitant medication).

• Cell savers: During the course of this trial, no cell savers will be used by participating patients.

• Escape medication: In case of a critical bleeding (by clinical judgment) during the liver transplantation procedure, treatment can be initiated in accordance with hospital guidelines and procedures e.g. antifibrinolytic drugs at habitual doses. All data on critical bleeding episodes should be reported as a serious adverse event. Type and amount of the escape medication and the justification will be recorded in the CRF.

• Enoxaparin or other low molecular weight heparin (LMWH): LMWH will be administered postoperatively as usual for deep venous thrombosis prophylaxis. Dosing will be according to routine local practice.

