## Methods/design

### Design and objectives

The study is designed as a multicenter, double blind, randomized placebo-controlled trial. The study is investigator-initiated.

The primary objective is to study the hemostatic efficacy of preoperative PCC administration in patients with cirrhosis and severe coagulopathy undergoing liver transplantation. The hemostatic efficacy will be primarily monitored by recording the need for RBC transfusion.

The secondary objective is to study the hemostatic safety of preoperative PCC administration in patients with cirrhosis undergoing liver transplantation. The hemostatic safety will be monitored by adverse event surveillance and laboratory measurements, with a special focus on thrombogenicity.

All study procedures during this study are summarized in Table 1.

**Table 1 T1:** Timing of study procedures

**Parameters**				**Timepoints**													
	**SEH**	**Surgical procedure**					**Postoperative days**										
		**Anesthesia**	**30 minutes after intervention**	**Pre-anhepatic phase**	**Anhepatic phase**	**Reperfusion phase**	**0/1**	**2**	**3**	**4**	**5**	**6**	**7**	**11**	**14**	**30**	
12-leads ECG	x	According to local protocol							x				x			
Lab	x						x	x	x	x	x	x	x		x	x
Troponin	x						x									
Plasma sample	x	x	**x**	**1 hour after intervention**	**15 minutes after start phase**	**15 minutes after start phase**	x		x		x			x		
				**2 hours after intervention**		**end of surgery**										
Viral safety	x															
TEG/ROTEM					**15 minutes after start phase**	**30 minutes after start phase**										
Blinded INR			**x**				x		x				x			
Ultrasound hepatic vessels		According to local protocol									first 24 h after surgery					
Registration transfusion products			**x**	**x**	**x**	**x**			x				x			
Physical examination with focus on thrombotic and ischemic events																

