#### Statistical analysis

Statistical analyses will be performed using the statistical software package SPSS 19.0 (SPSS Inc, Chicago, IL). Two-sided tests using the 5% critical level will be used throughout. The Mann–Whitney U test will be used to determine a significant difference in transfusion needs between the 2 groups. Intergroup categorical data will be compared using Chi-square or Fisher exact test. Intergroup continuous data will be analyzed with parametric or non-parametric analysis methods depending on the presence/absence of Gaussian distribution. If required, appropriate corrections for multiple comparisons will be applied. Independent risk factors for bleeding diathesis and transfusion during OLT will be identified using uni- and multivariate logistic regression analysis. All variables that reached a P < = 0.05 in the univariate analysis will be included in the multivariate linear regression analysis. P <0.05 will be considered statistically significant.

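### The primary comparison of RBC units ignores starting haematocrit, a prognostic baseline value under the fixed transfusion trigger; adjusting for it would recover some precision

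*Protocol article*

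**What the plan says.** All references are to the protocol article.

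- **Objective** (Design and objectives): "The hemostatic efficacy will be primarily monitored by recording the need for RBC transfusion".
- **Endpoint** (Endpoints): "The primary endpoint will be the number of RBC units transfused during the OLT procedure and in the 24 hour post-surgery period", the 24 hours running from arrival at the ICU.
- **Trigger and counting rule** (Transfusion guidelines): "RBC transfusions when hematocrit <25%: Adjustment can be performed at several time points; the units given before surgery do not count". The same bullet adds that "only those given during and directly after surgery (within 24 h of arrival at ICU) count for determination of endpoint", and that the number and volume of units go into the CRF.
- **Stratification** (Randomization and blinding): "We will stratify per center, and for patient age and gender".
- **Primary test** (Statistical analysis): "The Mann–Whitney U test will be used to determine a significant difference in transfusion needs between the 2 groups".
- **Only regression described** (Statistical analysis): "Independent risk factors for bleeding diathesis and transfusion during OLT will be identified using uni- and multivariate logistic regression analysis". It is a search for risk factors. It is not tied to the treatment comparison and does not name haematocrit.
- **Available data**: Table 1 marks a laboratory sample in the column before surgery, and Table 4 lists haematocrit among the laboratory parameters. A baseline value therefore appears to be collected, although the text around Table 4 speaks of postoperative days.

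**The concern.** The RBC count stands in for haemostatic efficacy. With a fixed haematocrit trigger it depends on two things: how much blood is lost, and how far the patient starts above 25%. Only the first can respond to prothrombin complex concentrate. A patient who starts just above the trigger is transfused early. One who starts well above it can lose a good deal of blood before the first unit is given.

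Starting haematocrit is thus prognostic for the endpoint by the protocol's own rule. It is not a stratification factor and it does not enter the primary test. At stake are some power that could be had from existing data, and protection if the arms happen to differ at baseline in a trial of 140 patients.

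**Working it through.** **1. The plan's own figure.** The Sample size section uses N = 16σ²/d² with SD 4 and d = 2: 16 × 16 / 4 = 64 per arm. The usual two-mean formula (two-sided 0.05, 80% power) gives 63, and 63 / 0.9 = 70. The stated 70 per group is reproduced. The check below uses 63 evaluable per arm.

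**2. Units per haematocrit point.** The documents give no blood volume, red-cell content per unit, or distribution of starting haematocrit. Assumed: blood volume 5 L, 0.18 L red cells per unit, mean starting haematocrit 31%, SD 5 points.

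- Linear: 5 × 0.01 / 0.18 = 0.278 unit per point.
- Isovolaemic dilution (blood lost at a higher haematocrit carries more red cells): the slope at 31% is 5 × 0.25 / (0.18 × 31%), with the haematocrit in points: 1.25 / (0.18 × 31) = 0.224 unit per point.

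**3. Variance explained,** R² = (SD of haematocrit × slope / 4)².

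- (5 × 0.224 / 4)² = 0.078
- (5 × 0.278 / 4)² = 0.121

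**4. Power with adjustment** = Φ(2 / (4 × √(1 − R²) × √(2/63)) − 1.96).

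| R² | Power |
|---|---|
| 0 | 80.1% |
| 0.078 | 83.2% |
| 0.121 | 84.9% |

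**5. Chance imbalance in arm means.** The standard error of the haematocrit difference is 5 × √(2/63) = 0.89 point. The 95% limit in units is 1.96 × 0.89 × 0.224 = 0.39 to 1.96 × 0.89 × 0.278 = 0.49.

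**6. Range.**

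| Assumption varied | R² | Power | 95% shift, units |
|---|---|---|---|
| Haematocrit SD 3 to 7 points, slope 0.224 to 0.278 | 0.03–0.24 | 81–90% | 0.2–0.7 |
| SD 5 points; 4 L with 0.20 L per unit up to 6 L with 0.16 L per unit, both slope formulas | 0.04–0.22 | 82–89% | 0.3–0.65 |

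**7. Simulation check** (4,000 trials per scenario, 63 per arm, alpha 0.05, Mann-Whitney against rank ANCOVA). The R² values in step 3 correspond to a correlation of about 0.28 to 0.35.

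| Correlation of haematocrit with units | Mann-Whitney power | Rank ANCOVA power |
|---|---|---|
| 0.3 | 76% | 79% |
| 0.4 | 78% | 83% |
| 0.5 | 78% | 87% |

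With no treatment effect, both tests rejected in about 5% of trials. In the roughly 16% of trials whose arms differed by more than 0.25 SD in haematocrit, the unadjusted test rejected in 8% (correlation 0.3) to 11% (correlation 0.5).

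**The case against.** The strongest reply is that nothing in the plan is invalid. Allocation is random, the surgical and anaesthesia teams are blinded, and study drug is given at most 30 minutes before incision, so starting haematocrit is essentially a pre-treatment variable. The Mann-Whitney test then holds its level overall. The 8 to 11% error rate applies only to trials selected for imbalance, and the p-value already allows for that possibility. All of this stands.

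Four stronger readings are tempting, and the documents do not support them:

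- **That the trial is underpowered for this reason.** The SD of 4 units comes from retrospective transfusion data at one centre. If units were counted there in a similar way, that SD already includes variation from starting haematocrit. Adjustment would add power above plan.
- **That starting haematocrit can outweigh the 2-unit effect.** Two patients starting at 26% and 36% may differ by 10 × 0.278 = 2.8 units on the linear rule, or 5 × 0.25 × ln(36/26) / 0.18 = 2.3 units under isovolaemic dilution. That contrasts two extreme patients. The target is a difference in arm means, for which the relevant figure is the 0.4 to 0.5 unit in step 5.
- **That leaving out pre-surgery units is a flaw.** Units given before surgery cannot reflect a drug given at induction, so excluding them is appropriate. Topping up patients below the trigger may even narrow the spread of starting values.
- **That pre-surgery units go unrecorded.** The RBC bullet sends units and volume to the CRF. The list under Parameters during surgery covers only surgery and the first 24 hours, so the point is unclear, but absence is not shown.

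An analysis plan that is not shown might add an adjusted analysis. The article nevertheless names the unadjusted test for the comparison of transfusion needs.

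**Conclusion.** The point holds as a modest improvement in precision. The endpoint depends partly on starting haematocrit because of the fixed trigger, and neither the stratification nor the named test uses that value. On the central assumptions, adjustment is worth 3 to 5 percentage points of power and guards against a chance shift of up to about a quarter of the target effect (0.49 / 2 = 0.24).

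The direction follows from the protocol's trigger rule. The size rests on the assumed haematocrit SD, blood volume and red-cell content per unit, none of which the documents give. The case does not rest on bias, an inflated overall error rate or a faulty sample size.

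**What to change.** In Statistical analysis, prespecify the primary comparison of RBC units as a rank ANCOVA or a proportional-odds model. The terms would be treatment, the last available haematocrit before study drug (at minimum the admission value) and the stratification factors: centre, age and gender. Keep the unadjusted Mann-Whitney test as a supportive analysis. Settle this before the interim analysis, so that the choice cannot depend on unblinded results.

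Leave the endpoint's exclusion of pre-surgery units as it is. State that such units are noted in the CRF where given, and confirm that the admission sample includes haematocrit. No change to the transfusion rule is implied.

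The cost is mainly wording. The primary estimate becomes a model-based odds ratio or an adjusted rank difference, which is less simple to report. The admission haematocrit may also miss a later pre-surgery top-up, because a value after such a top-up is not a scheduled measurement. Adjustment would then recover somewhat less precision, but it would remain valid.
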